## LIST OF ABBREVIATIONS AND RELEVANT DEFINITIONS

|                  |                                                                                                                                                                                                                               |
|------------------|-------------------------------------------------------------------------------------------------------------------------------------------------------------------------------------------------------------------------------|
| ABR       | General Assessment and Registration form (ABR form), the application form that is required for submission to the accredited Ethics Committee; in Dutch: Algemeen Beoordelings- en Registratieformulier (ABR-formulier) |
| AE        | Adverse Event                                                                                                                                                                                                          |
| AHEP      | Amsterdam Hearing Evaluation Plot                                                                                                                                                                                      |
| AR        | Adverse Reaction                                                                                                                                                                                                       |
| CA        | Competent Authority                                                                                                                                                                                                    |
| CCMO      | Central Committee on Research Involving Human Subjects; in Dutch: Centrale Commissie Mensgebonden Onderzoek                                                                                                            |
| CLEAR-EAR | ChoLEsteatomA Recidivism – Evaluation And Recommendations                                                                                                                    |
| CV        | Curriculum Vitae                                                                                                                                                                                                       |
| CWD       | Canal wall down                                                                                                                                                                                                        |
| CWU       | Canal wall up                                                                                                                                                                                                          |
| DSMB      | Data Safety Monitoring Board                                                                                                                                                                                           |
| DW-MRI    | Diffusion-weighted magnetic resonance imaging                                                                                                                                                                          |
| EU        | European Union                                                                                                                                                                                                         |
| EudraCT   | European drug regulatory affairs Clinical Trials                                                                                                                                                                       |
| ENT       | Ear-Nose-Throat                                                                                                                                                                                                        |
| EQ-5D-5L  | EuroQol-5 Dimensions                                                                                                                                                                                                   |
| GCP       | Good Clinical Practice                                                                                                                                                                                                 |
| GDPR      | General Data Protection Regulation; in Dutch: Algemene Verordening Gegevensbescherming (AVG)                                                                                                                           |
| HUI3      | Health Utility Index - 3                                                                                                                                                                                               |
| IB        | Investigator's Brochure                                                                                                                                                                                                |
| IC        | Informed Consent                                                                                                                                                                                                       |
| iMCQ      | Medical Consumption Questionnaire                                                                                                                                                                                      |
| IMP       | Investigational Medicinal Product                                                                                                                                                                                      |
| IMPD      | Investigational Medicinal Product Dossier                                                                                                                                                                              |
| iPCQ      | Productivity Cost Questionnaire                                                                                                                                                                                        |
| ITT       | Intention-to-treat analysis                                                                                                                                                                                            |
| METC      | Medical research ethics committee (MREC); in Dutch: medisch-ethische toetsingscommissie (METC)                                                                                                                         |
| OQUA      | Otology Questionnaire Amsterdam                                                                                                                                                                                        |

|                   |                                                                                                                                                                                                                                                                                                                                                  |
|-------------------|--------------------------------------------------------------------------------------------------------------------------------------------------------------------------------------------------------------------------------------------------------------------------------------------------------------------------------------------------|
| PROM       | Patient-reported outcome measure                                                                                                                                                                                                                                                                                                          |
| PSA        | Probabilistic sensitivity analysis                                                                                                                                                                                                                                                                                                        |
| Recidivism | Total number/rate of residual and recurrent disease                                                                                                                                                                                                                                                                                       |
| (S)AE      | (Serious) Adverse Event                                                                                                                                                                                                                                                                                                                   |
| SPC        | Summary of Product Characteristics; in Dutch: officiële productinformatie IB1-tekst                                                                                                                                                                                                                                                       |
| Sponsor    | The sponsor is the party that commissions the organisation or performance of the research, for example a pharmaceutical company, academic hospital, scientific organisation or investigator. A party that provides funding for a study but does not commission it is not regarded as the sponsor, but referred to as a subsidising party. |
| SUSAR      | Suspected Unexpected Serious Adverse Reaction                                                                                                                                                                                                                                                                                             |
| UAVG       | Dutch Act on Implementation of the General Data Protection Regulation; in Dutch: Uitvoeringswet AVG                                                                                                                                                                                                                                       |
| WMO        | Medical Research Involving Human Subjects Act; in Dutch: Wet Medisch-wetenschappelijk Onderzoek met Mensen                                                                                                                                                                                                                                |

## SUMMARY

**Rationale:** The mainstay of cholesteatoma treatment is surgery with effective and safe removal of the disease as the principal goal. New techniques find their way in the international otologic community by proving lower recurrent and residual disease rates compared to the conventional techniques. One newly implemented and previously described technique is the obliteration technique of the mastoid. Although this approach has become more popular in recent years, high-quality evidence is missing.

**Objective:** The primary aim of this study is to investigate whether a canal wall up (CWU) tympanomastoidectomy with obliteration of the mastoid and paratympanic or epitympanic spaces reduces cholesteatoma recurrence and residual rates compared to the same approach without obliteration. Secondly, hearing outcomes after both surgical techniques are compared to investigate whether one of the two results in superior postoperative hearing. The quality of life will be measured using the Otology Questionnaire Amsterdam (OQUA). The economic evaluation will involve collecting the EQ-5D-5L, HUI-3, iPCQ and iMCQ questionnaires as well as direct intervention costs from the sponsoring centre.

**Study design:** The proposed study is a single-blind randomized controlled trial. One hundred seventy-eight patients will be included. Patients are randomized into one of two groups in an equal 1:1 allocation ratio. The randomization will be centre-stratified and a 4,6,8 block randomization will be used.

**Study population:** Patients above the age of 18 who undergo a CWU approach for removal of cholesteatoma in one of the participating centres.

**Intervention (if applicable):** Group A will undergo a CWU approach without obliteration and group B a CWU approach with obliteration.

**Main study parameters/endpoints:** Rates of recurrent or residual cholesteatoma are evaluated by diffusion-weighted magnetic resonance imaging (DW-MRI) and micro-otoscopy after approximately one, three and five years. If diffusion restriction is seen on DW-MRI and/or retraction of the tympanic membrane is seen during micro-otoscopy, suspicion for recurrent or residual disease will be recorded. To confirm the diagnosis and to determine whether the cholesteatoma is either recurrent or residual, we will analyse the tympanic membrane description at the beginning of the revision surgery. All other surgical outcome measures are recorded in the surgical report. Pure tone audiograms, including air and bone conduction, and speech recognition scores are evaluated pre- and postoperatively for each patient. The EQ-5D-5L, HUI-3, iMCQ and iPCQ questionnaires will be filled in once pre- and a two times postoperatively by every patient. The OQUA will be filled in once preoperatively and three times postoperatively. The direct health-care costs will be recorded for the sponsor centre and extrapolated for the whole trial.

**Nature and extent of the burden and risks associated with participation, benefit and group relatedness:** The burden patients will experience by participating in this study will be filling in the questionnaire multiple times. The surgery, along with the imaging procedures (CT and DW-MRI), audiometry and follow-up appointments, is part of standard care and takes place irrespective of participation in this study.

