The goal of cholesteatoma treatment is to eradicate the disease and create a safe and dry ear, while preventing recurrence of pathology and preserving, or even optimizing, hearing. The best surgical approach has been subject of debate for decades. The two traditional approaches are: canal wall down (CWD) and canal wall up (CWU) tympanomastoidectomy. Although they both have their advantages and disadvantages, the CWU technique has increasingly become the standard approach. CWD surgery results in a radical cavity, which gives a wide visual exposure of the disease for removal and therefore minimizes the chance of leaving cholesteatoma behind. However, a radical cavity creates a situation that requires regular debridement, increased risk of recurrent infections, and makes the fitting of hearing aids more challenging. The CWU approach on the contrary, maintains the normal anatomy of the bony part of the ear canal. It results in less frequent inflammations, hearing aids fit better and the regular outpatient cleaning of the ear is not indicated (1,2). However, the major issue with the CWU treatment is the higher odds of recurrent and residual disease. Whereas CWD tympanomastoidectomy show recidivism - including both recurrent and residual disease - rates of 0 to 17%, CWU tympanomastoidectomy rates vary between 9% and 70% (3,4).

Over the past decade, there has been growing interest in finding ways to decrease the disease recurrence rates and improve post-operative hearing outcomes. One promising technique is the obliteration of the mastoid and epitympanic area after either CWD or CWU tympanomastoidectomy. Obliteration is the act of filling the cavity that is created to reach the middle ear with either bone dust (sometimes also referred to as bone pâté) or artificial material. The purpose is to create a situation in which the obliteration material prevents the tympanic membrane from retracting and therefore lowers the chance of cholesteatoma recurrence. Mercke was one of the first otologic surgeons to present promising outcomes after obliteration in combination with CWD tympanomastoidectomy (5).

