All pre-operative measurements are part of standard care in the Netherlands and Belgium. Pre-operatively patients receive an audiometric exam, a physical examination of the ear, a CT-scan and fill in the patient-reported outcome measure (PROM). Follow-up will be planned at least at 6-18 weeks, at around 1 year and at around 3 years after surgery. It is important to note that conducting a CT scan and audiometry preoperatively as well as the DW-MRI's after 1 and 3 years are part of the standard care. In line with standard care, if there is a suspicion for recurrent or residual pathology (either clinically by micro-otoscopy or radiologically by DW-MRI) the treating physician will perform a revision surgery. If during revision surgery the suspicion is confirmed, the type of recidivism (residual or recurrent) is recorded and the follow-up of the patient ends. Data that is collected up until the point of detection of residual or recurrent disease will be used for analysis (this is not an exclusion criterium). If the suspicion is not confirmed (false-positive) then the patient will continue the follow-up as planned (unless a reconstructive procedure with the goal of improving hearing has been performed). During the three years of follow-up, patients should not undergo another type of ear surgery. If this is unavoidable, as judged by the treating physicians, the patient will be retrospectively excluded. In order to ensure that the same surgical data is collected in all participating centers, a standardized operation report will be written and shared by the sponsor (UMC Utrecht). This operation report will be recorded in the electronic patient dossier (with the exception of the information if obliteration was used or not) and transferred to Castor EDC. In Castor there will be a variable to also record if obliteration has taken place or not. The only methodology that is different to standard care is the randomization of the patients and the completion of the questionnaire. It is important to note that the technique used for the obliteration technique differs slightly between centers. The exact surgical technique will be described by the participating otologists and included in the description of the study, for example in a publication.

**Figure 1.** Flowchart of the study. *Standard care is indicated by \**[figure not shown]

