## 6. METHODS

### 6.1 Study parameters/endpoints

#### 6.1.1 Main study parameter/endpoint

The main endpoint is the number of patients with recurrent or residual cholesteatoma. Follow-up for recurrent/residual cholesteatoma will be performed after 6-18 weeks and after approximately 1, 3 and 5 years. Follow-up is done by micro-otoscopy and DW-MRI scans (after 1, 3 and 5 years) (see figure 1 for the follow-up steps). A newly formed retraction pocket from the tympanic membrane correlates with recurrent disease (clinical diagnosis), whereas cholesteatoma formation behind a normal or an intact tympanic membrane after primary surgery correlates with residual disease (radiologic diagnosis).

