### **8.1 Primary study parameter(s)**

The data of our primary outcome are quantitative and will be presented as frequencies and proportions. To compare the difference in recidivism (recurrent and residual disease) at 12, 36 and 60 months between both surgical groups the Chi-squared test or Fisher's exact test will be used. The relative risk (RR) and absolute risk difference (RD) will be calculated as effect sizes using a generalized linear model for binomial outcome with a log-link (for RR) and identity link (RD). The primary analysis will be adjusted for site by including centre as covariate in a logistic regression model with treatment arm as the main predictor. All effect sizes will be accompanied by 95% confidence intervals. To graphically demonstrate the rates of recidivism, recurrent and residual disease over the follow-up time, a Kaplan-Meier analysis will also be performed and survival curves will be constructed. Multiple imputation will be used to deal with missing

outcomes. A 20% difference is defined as the threshold for clinical relevance and will be consistently applied in both clinical effectiveness analyses and the health economic evaluation.

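### Recidivism is typed from the tympanic membrane, which obliteration is meant to change, so the separate recurrent and residual rates (not the composite) can be distorted by arm

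*Protocol*

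**What the plan says.** **Typing and confirmation (Protocol, Summary, main study parameters).** Diffusion restriction on DW-MRI, a retracted membrane at micro-otoscopy, or both raise the suspicion. Then: "To confirm the diagnosis and to determine whether the cholesteatoma is either recurrent or residual, we will analyse the tympanic membrane description" as it stands when the revision begins. One observation thus serves to confirm disease and to type it.

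**Mapping (Section 6.1.1).** A new retraction pocket goes with recurrent disease. For the other type, "cholesteatoma formation behind a normal or an intact tympanic membrane after primary surgery correlates with residual disease".

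**Effect of treatment on that sign (Introduction).** On obliteration: "The purpose is to create a situation in which the obliteration material prevents the tympanic membrane from retracting", and so to lower the chance of recurrence.

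**Recording (Section 3).** "If during revision surgery the suspicion is confirmed, the type of recidivism (residual or recurrent) is recorded", after which follow-up ends. A suspicion not borne out at revision is a false positive, and follow-up then normally continues. No typing criterion and no mixed category appear there.

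**Use.** The main endpoint in Section 6.1.1 is recurrent or residual disease combined, and the tests and effect sizes in Section 8.1 use recidivism as a whole. The components appear in the wording of the primary objective (Section 2) and in the Kaplan-Meier display of Section 8.1: "To graphically demonstrate the rates of recidivism, recurrent and residual disease over the follow-up time". Under Section 6.2 only participants are blinded.

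**The concern.** The sign that decides the label is one that the intervention is designed to alter. Take the same residual focus in two ears. Without obliteration the membrane may also have formed a retraction pocket, and the event is then typed recurrent. With obliteration the membrane may have stayed in place, and the event is typed residual. If this happens more often in one arm, the fall in recurrent disease is overstated and residual disease appears to be in excess after obliteration, with no true difference in residual disease. Because follow-up ends at confirmation, later observation within the trial will not correct the label.

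The split matters to readers. The primary objective names both rates, the Introduction reports them separately from the literature, and it describes the worry that disease left behind is harder to detect after obliteration.

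There is a second, separate problem. A membrane description cannot show whether cholesteatoma is present deeper in the ear, so it cannot serve as confirmation. Retraction is also one of the signs that raises the suspicion, which makes its use as confirmation circular.

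**Working it through.** **1. The plan's own figure (Section 4.4).** Inputs: 20% v 40%, 80 per arm, two-sided Z test with pooled variance, alpha 0.05. Exact binomial enumeration gives power 0.8009 and, at a common rate of 40%, actual alpha 0.0472. Both match the table. With 79 per arm power is 0.795. Dropout: 160 / 0.90 = 177.8, so 178. The calculation reproduces, and it rests on the composite.

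**2. Effect of typing on the rates.** In one arm let r be the true residual rate, c the true recurrent rate, and q the share of residual cases with a coexisting retraction pocket that are typed recurrent.

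- Typed residual = r(1 − q)
- Typed recurrent = c + rq
- Sum = r + c, whatever q is

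The composite cannot move. With equal r in both arms, the false residual difference (obliteration minus none) is r(q_none − q_obl), and the recurrent difference shifts by the same amount in the opposite direction.

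**3. Numbers.** The protocol gives neither q nor r for this trial, so all of the following are assumptions.

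With r = 8% in both arms:

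| q, none v obliteration | Typed residual, none v obliteration | Ratio |
|---|---|---|
| 50% v 10% | 0.08 × 0.50 = 4.0% v 0.08 × 0.90 = 7.2% | 1.80 |
| 30% v 5% | 0.08 × 0.70 = 5.6% v 0.08 × 0.95 = 7.6% | 1.36 |
| 50% v 30% | 0.08 × 0.50 = 4.0% v 0.08 × 0.70 = 5.6% | 1.40 |

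In patients, the first row at 80 per arm is 80 × 0.040 = 3.2 v 80 × 0.072 = 5.8. With r = 4.2%, the residual rate that the Introduction cites for canal wall up surgery with obliteration, it is 80 × 0.042 × 0.50 = 1.7 v 80 × 0.042 × 0.90 = 3.0, a shift of about 1.3 patients.

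Now hold the composite at the design values of 40% v 20% with equal r, so that the true residual difference is 0 and the true recurrent difference is −20 points:

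| r | q, none v obliteration | Typed residual difference | Typed recurrent difference |
|---|---|---|---|
| any | 0 v 0 | 0 | −20 points |
| 10% | 20% v 20% | 0 | −20 points |
| 5% | 20% v 5% | +0.75 points | −20.75 points |
| 10% | 40% v 10% | +3 points | −23 points |
| 15% | 60% v 10% | +7.5 points | −27.5 points |

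In the 20% v 20% row each arm's own component rates still shift (residual from 10% to 8%), but the comparison between arms does not.

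**4. Confirmation, side by side.** The Summary confirms from the membrane. Under Section 6.1.1 a normal or intact membrane is compatible with residual disease. An ear with a false-positive DW-MRI can have the same membrane. The Summary's criterion therefore cannot separate the two. Section 3 has the suspicion confirmed, or not, during the revision itself, which can separate them. The two statements need to agree.

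**The case against.** The strongest reply is that the primary result is untouched. The list of abbreviations defines recidivism as the total of both types, Section 4.4 describes the primary objective as residual or recurrent disease, and the test and sample size use the composite. The components are shown only as curves, with no component test stated. All of this stands.

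The wording can also be read less strictly. The Summary does not say that the membrane is the sole criterion, Section 6.1.1 speaks of correlation, and its sign is a new retraction pocket rather than any retraction. Section 6.1.2 collects the findings of every revision. This softens the point, but the protocol offers no other typing criterion and no rule for an ear with both.

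Three stronger readings might be inferred, and the documents do not support them.

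- *Both component rates are biased.* Distortion between arms needs residual disease to coexist with retraction at a different frequency in each arm. The protocol gives no such frequency, and with none there is no distortion. Part of any fall in recurrent labels would also be the intended effect, since on the protocol's account recurrence arises from retraction.
- *False positives can never be recognised.* Section 3 provides for them and records the type only after confirmation.
- *The confirmation rule biases the composite.* Taken literally and alone the Summary sentence could do so, because retraction is expected to differ by arm. Section 3 indicates that this is not how events are to be established.

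Finally, typing by continuity with a retraction pocket is still a judgement by an unblinded surgeon, made once the obliteration is visible. That is fair, and it is a limit of the remedy.

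**Conclusion.** The point holds in a limited form. The typing sign is a target of the intervention, no label exists for both types, and the Summary and Section 3 disagree on what confirms an event. The separate recurrent and residual curves, and any statement that each rate was reduced, can therefore be distorted by arm.

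The direction follows if coexisting retraction is more frequent without obliteration: too few residual labels in that arm, and too large an apparent fall in recurrence. The size is unknown. With equal true residual rates of 5% to 15% and the unequal coexistence shares tried above, the false residual difference is 0.75 to 7.5 points. In the 8% illustration with 50% v 10% coexistence it is 3.2 points, or between two and three patients at 80 per arm. It is zero if the two never coexist, or if coexistence and residual rates are equal in both arms.

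Typing does not affect the composite endpoint, its test, its power or the 178 patients. This is a low-cost improvement to the endpoint definition and does not threaten the primary analysis.

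**What to change.** 1. **Confirmation.** Align the Summary with Section 3, so that an event counts as confirmed when cholesteatoma is found at the revision.
2. **Typing.** In the Summary and Section 6.1.1, type each event from the operative findings that Section 6.1.2 already collects: continuous with a retraction pocket (recurrent), separate from the membrane (residual), or both. Keep the membrane description at the start of revision as a separate descriptive item.
3. **Status of the components.** State in Section 8.1 that only composite recidivism is confirmatory and that the recurrent and residual rates are descriptive, and word the objective in Section 2 to match.

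The cost is protocol wording and one extra category in the Castor revision form, with no added visits or procedures. The downside is that typing remains a judgement by the unblinded surgeon, as the membrane description already is. It is best settled before revisions accumulate, since a split recorded only from the membrane may not be recoverable later.
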